### 2.9. Monitoring

A data monitoring committee will be set up during the study recruitment period. Interim analyses will be supplied to the committee in strict confidence, together with any other analyses that the committee may request. Based on the data monitoring committee’s advice, the trial steering members will decide whether or not to modify the trial intake.

In our study, an adverse event will be defined as any untoward medical occurrence in a subject without regard to the possibility of a causal relationship. Adverse events will be collected after the subject has provided consent and enrolled in the study. If a subject experiences an adverse event after the informed consent document is signed (entry) but the subject has not started to receive study intervention, the event will be reported as not being related to the study’s exercise program. For this study, the following will be considered serious adverse events: severe or permanent disability, use of prohibited substances and any other significant hazard as determined by the study members. Serious adverse events occurring after a subject has stopped participating in the study will not be reported unless the researchers feel that the event may have been caused by the study protocol procedure.

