### 2.2. Eligibility Criteria

The inclusion criteria for participating in the program will be: (i) to belong to the Spanish Athletics Federation; (ii) to have been training and competing in Spanish Athletics Federation competitions for at least two years; and iii) to be in the first third of the classification for the last five races of the previous season. Regarding the exclusion criteria, the following will be taken into account: (i) having cardiovascular pathologies, abnormal blood pressure parameters or diagnosed respiratory problems; (ii) being treated for psychological problems, or regularly taking a drug(s) that has a direct or indirect effect on the nervous system (e.g., anxiolytics, antidepressants or neuroleptics); (iii) substance use that is not permitted by the International Association of Athletics Federations (IAAF); (iv) occasional consumption of medication for a disease related to the cardiorespiratory system (e.g., influenza) that might alter performance and (v) not performing at least 90% of the workouts during the intervention.

The trial steering members will be responsible for checking that the subjects interviewed meet the inclusion criteria. The Spanish Athletics Federation’s medical team will certify that the subjects do not meet any of the exclusion criteria. After being informed of the study design and potential risks, all athletes will sign a written informed consent document. The model consent form is shown in Appendix A.

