The incremental treadmill test will be performed by the Physical Exercise and Human Performance Research Group at the University of Murcia (Spain). This is a more objective way of determining physical fitness and represents the maximal performance capacity of an individual [39]. First, with the athlete in the supine position, a cardiovascular examination will be carried out at rest by means of cardiac auscultation, blood pressure and an electrocardiogram (ECG). The electrodes for recording the ECG and heart rate will be kept in place throughout the test. The Cardioline Cube^®^ electrocardiograph will be used. To perform the incremental treadmill test, the Runner srl (Cavezzo Italy) treadmill will be used, as it was in other studies such as Ballesta-García, Martínez-González-Moro, Ramos-Campo, and Carrasco-Poyatos [40]. Similar to other studies, such as Nuuttila et al. [30] or Vesterinen et al. [31], a prior 2-min aerobic warm up will be performed at 6 km/h. The test itself will start at a velocity of 7 km/h. The speed will be increased by 0.1 km/h every 6 s. The incline will remain at 1% throughout the test. The athletes will be encouraged to perform at maximum effort. The test will end when the subject can no longer run; the subject will indicate this with a hand gesture. The recovery phase will then begin at 4km/h for 3 min followed by rest for a further 2 min. The tests will be considered maximal and valid when the theoretical heart rate (220-age) exceeds 85% and the respiratory exchange ratio (RER) is greater than 1.15 [41]. During the stress test, the subjects will breathe through a mask connected to a gas analyzer (Metalyzer 3b^®^, Cortex, Leipzig, Germany). All gas exchange parameters will be measured breath-by-breath and averaged every 30 s. The VO_2max_ will be defined as the oxygen consumption plateau [42]. The aerobic (VT1) and anaerobic (VT2) thresholds will be determined. Before each test, the gas analyzer will be manually calibrated. The test’s maximal speed (V_max_), maximal heart rate (HR_max_), and respiratory exchange ratio (RER) will be recorded. The V_max_ or HR_max_ will be defined as the highest speed, or heart rate, reached for a finished stage. The speed, heart rate, respiratory exchange ratio and VO_2_ at each ventilatory threshold will also be recorded as V_VT1,_ V_VT2_, HR_VT1_, HR_VT2_, RER_VT1_, RER_VT2_, VO_2VT1_, and VO_2VT2_, respectively. All tests will be carried out under similar environmental conditions (an ambient temperature of 20–22 degrees).

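### The serious adverse event rule names prohibited-substance use, which is not a medical event, and leaves death, life-threatening events and hospital admission to the study members' discretion

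*Protocol article*

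**What the plan says.** The rule is in section 2.9 (Monitoring) of the protocol article. The broad definition comes first: "an adverse event will be defined as any untoward medical occurrence in a subject without regard to the possibility of a causal relationship". Collection starts after consent and enrolment.

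The seriousness rule then has three items: "severe or permanent disability, use of prohibited substances and any other significant hazard as determined by the study members". The section does not define a significant hazard or say who the study members are.

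One later rule uses the label: "Serious adverse events occurring after a subject has stopped participating in the study will not be reported unless the researchers feel that the event". The condition that completes this sentence is a suspected link with a study procedure.

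Two other sections bear on the point. Section 2.2 (Eligibility Criteria) makes use of substances banned by the athletics federation the third exclusion criterion. Section 2.4 (Outcomes) has each athlete run a treadmill test with ECG electrodes in place until exhaustion ("The test will end when the subject can no longer run; the subject will indicate this with a hand gesture") and, in a separate session, 3000 m at maximum speed.

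**The concern.** A serious adverse event should be an adverse event that meets a further criterion of gravity. Here the two definitions do not nest. One named item is a matter of conduct and need involve no medical occurrence. Three kinds of grave medical event are not named at all.

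The result is an odd ordering. Substance use that harms nobody is serious automatically. A collapse during a maximal test that leads to admission and full recovery is serious only if someone decides that it was a significant hazard. What is at stake is whether the serious label means the same thing from one event to the next and whether it tracks medical harm.

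**Working it through.** No formula applies and the plan gives no figure to reproduce. The check sets the two definitions in section 2.9 side by side and runs typical events through both.

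**Step 1. Split the seriousness rule into its items.** There are three:

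1. Disability that is severe or permanent: named, a medical outcome.
2. Prohibited-substance use: named, a matter of conduct.
3. Any other significant hazard: not specified, decided by the study members.

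**Step 2. Look for a criterion elsewhere.** No other section of the article gives a seriousness criterion or refers to an outside definition. Death, threat to life and hospital admission appear nowhere as criteria. The consent appendix is not shown and could not be checked.

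**Step 3. Classify events under both definitions as written.**

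| Event | Adverse event? | Serious? |
|---|---|---|
| Severe or permanent disability | Yes | Yes, named |
| Prohibited-substance use, no medical consequence | No, not a medical occurrence | Yes, named |
| Death, not preceded by such disability | Yes | Only by discretion |
| Life-threatening event, full recovery | Yes | Only by discretion |
| Hospital admission, full recovery | Yes | Only by discretion |

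Of the three unlisted categories, 0 of 3 are named. The second row is the internal contradiction: an event can be a serious adverse event without being an adverse event. It follows from the article's own wording and needs no outside standard.

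**Step 4. Ask what depends on the label.** In the text shown, one rule does: serious events after participation ends are reported only if the researchers suspect a link with a study procedure. The article does not say what happens to non-serious events after that point. If they are not reported (an assumption), a late admission would have to pass two judgements before being reported: that it was a significant hazard, and that the study may have caused it. During participation, every event in the table that is an adverse event is collected whatever its label.

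**The case against.** The other side has a substantial case.

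- **The list is open.** Its last item can take in any grave event, and it is hard to imagine study members leaving out a death. A reader might infer that the unlisted events can never be serious; the wording does not support that.
- **Nothing drops out of collection during participation.** The broad definition "any untoward medical occurrence in a subject without regard to the possibility of a causal relationship" captures all of these medical events. Only the label is discretionary.
- **Flagging substance use may be deliberate.** The rule is stated to be for this study, in federated athletes. The exclusion criterion governs entry and the seriousness item can cover later conduct, so the two do not contradict each other. The article describes no testing for substances, so nothing should be built on a positive test.
- **Risk is screened.** Section 2.2 excludes cardiovascular disease, abnormal blood pressure and diagnosed respiratory problems. Section 2.4 requires auscultation, blood pressure and a resting ECG before the treadmill test.
- **No passage ties the trial to a particular seriousness standard**, and any replacement list will keep some judgement.

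Two stronger readings are tempting. One is that the serious event rate would be biased between arms, with a single event moving an arm of 7 by 1/7 = 14.3 percentage points. Section 2.8 (Data Analysis) plans no comparison of serious events, so that figure describes the arm size and measures nothing in the plan. The other is that the people judging hazard know the allocation. Section 2.3 (Interventions) has the steering members calculate HRV and inform the HRV-G coach, and section 2.7 (Allocation and Blinding) names only the athletes and the data monitoring committee as blinded. But section 2.9 speaks of study members, and nothing says that these are the same people. Bias is a possibility, not a finding.

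What survives is narrower. Screening lowers the chance of an event but does not classify one that occurs. Likely good sense by the study members does not replace a stated criterion. A sport-specific reason for recording substance use does not make it a medical occurrence.

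**Conclusion.** The point holds as a defect in safety classification. The article writes the seriousness rule out in full, so this is a rule stated badly and not a detail left to a longer protocol. It conflicts with the adverse event definition in the same section on substance use, and it leaves death, life-threatening events and hospital admission to undefined discretion unless severe or permanent disability is involved.

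The defect is small. Severe or permanent disability, itself a grave outcome, is named. The unlisted medical events are still collected as adverse events. Sample size, power, significance level and the planned efficacy analyses are untouched, and no numerical magnitude attaches to it. The conclusion assumes that no other trial document, including the consent appendix, supplies a different definition. It is worth correcting because the correction costs little.

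**What to change.** In section 2.9, define a serious adverse event as an adverse event, in the plan's own sense, with one of these medical outcomes: death; a life-threatening event; hospital admission or its prolongation; persistent or significant disability. Keep a discretionary item, limited to other medically important events, so that judgement is used for the unclear cases only.

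Record prohibited-substance use as an eligibility or protocol deviation, and as an adverse event only if it causes a medical occurrence. It is then classed as serious on the same outcome criteria as any other event.

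The cost is a reworded definition in the protocol and a matching change to the adverse event form, with no extra visits or staff. The downside is that slightly more events may be classed as serious.

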### 2.3. Interventions

Based on the methodology used by Javaloyes et al. [24] and Vesterinen et al. [31], the intervention will be divided into two training periods for both study groups (HRV-G and TRAD-G): a four-week preparation period (PR) and an eight-week training period (TR). Both will maintain the weekly training volume. The training carried out will mainly be running. The PR period will be common to both groups and will be a familiarization phase for the training sessions and their intensities. During this period, the training intensity will gradually increase for the first three weeks and then decrease in the fourth week. This will mean three weeks of overloading and one week of recovery (3:1). The training to be carried out by the athletes is presented in more detail in Table 1. In the TR period, each group will carry out the corresponding intervention. The TRAD-G group will train according to a predefined training program, which will include sessions carried out at low intensity (approximately 50% of the total), and other sessions of moderate and high intensity, with a structure similar to that carried out during the PR period (Table 2). The training prescribed to the HRV-G group will depend on the subjects’ HRV, in accordance with authors such as Javaloyes et al. [24], Kiviniemi, Hautala, Kinnunen, and Tulppo [34], and Lamberts, Swart, Noakes, and Lambert [35].

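### After an athlete stops, serious adverse events are reported only if the researchers suspect a causal link, which is narrower than the protocol's own cause-free definition

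*Protocol article*

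**What the plan says.** Four statements in section 2.9 (Monitoring) of the protocol article matter here.

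- **Definition.** The article states that "an adverse event will be defined as any untoward medical occurrence in a subject without regard to the possibility of a causal relationship".
- **Start of collection.** "Adverse events will be collected after the subject has provided consent and enrolled in the study".
- **Between consent and the start of the intervention.** Events are kept, but their attribution is set in advance: "the event will be reported as not being related to the" exercise programme.
- **After an athlete stops.** "Serious adverse events occurring after a subject has stopped participating in the study will not be reported unless the researchers feel". The sentence goes on to except only those events which, in their view, the trial's procedures could have brought about.

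Three other sections bear on the last rule. Section 2.2 lists completing fewer than 90% of the workouts as an exclusion criterion, although this can only be known during the trial. Section 2.7 names the athletes and the data monitoring committee as blinded, and nobody else. Section 2.8 applies intention-to-treat to all data, with last observation carried forward.

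**The concern.** The definition removes cause from the question of what counts as an event. The post-stop sentence brings it back as the condition for reporting. The two can stand together on paper, but in practice the second undercuts the first for one group: athletes who leave early.

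That group matters for safety. An athlete with an overload injury misses sessions and may leave or be excluded because of it. One of the protocol's serious categories is disability that is severe or lasting, and whether an injury is lasting is often clear only some time after training has ceased. The rule can therefore fall on the period when an injury turns out to be serious.

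Section 3 (Discussion) presents the expected findings as relevant to overuse and injury risk, and states the expectation that HRV-G will perform better. A safety record that depends on opinion about cause is a weak base for remarks on injury.

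**Working it through.** No figure in the plan needs reproducing. The check sets the rules side by side and then asks how easily an athlete could come under the post-stop rule.

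**1. Event status by time of onset (section 2.9)**

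| Onset | Reported? | Role of cause |
|---|---|---|
| After consent, before the intervention | Yes | Attribution preset as unrelated |
| During participation | Yes | None stated as a condition |
| After stopping, serious | No by default | Reported only if researchers think the study may be responsible |

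Only the last row makes reporting depend on cause. It does not separate an athlete who has completed week 12 from one who leaves in, say, week 7. For completers, a cause-based rule after the end of study is defensible. For early leavers it operates inside the planned observation period.

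**2. How few missed sessions breach the 90% rule**

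Inputs are Tables 1 and 2, assuming one session per filled moderate- or high-intensity cell. Table 2 covers TRAD-G only, because HRV-G sessions in the training period are not tabulated.

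- Preparation period (PR), weeks 1–4: moderate/high 1 + 2 + 3 + 0 = 6. Low, minimum: 3 + 2 + 2 + 3 = 10; maximum: 4 + 3 + 3 + 4 = 14. Total 16 to 20.
- Training period (TR), weeks 5–12: moderate/high 1 + 2 + 3 + 0 + 1 + 1 + 3 + 0 = 11. Low, minimum: 3 + 2 + 2 + 3 + 3 + 2 + 2 + 3 = 20; maximum: 4 + 3 + 3 + 4 + 4 + 3 + 3 + 4 = 28. Total 31 to 39.
- All 12 weeks: 47 to 59.

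Missed sessions that take an athlete below 90%:

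- 47 planned: missing 5 gives 42/47 = 89.4%; missing 4 gives 43/47 = 91.5%.
- 59 planned: missing 6 gives 53/59 = 89.8%; missing 5 gives 54/59 = 91.5%.

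So 5 or 6 missed sessions are enough. The tables prescribe 3 to 6 sessions a week, so this is about one to two weeks off. An ordinary running injury could do it. The article does not say outright that an athlete excluded under this rule has stopped participating; that step is an inference, though a natural one.

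**3. Who judges cause**

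Section 2.9 says the researchers. They are not among those named as blinded in section 2.7. Section 2.3 shows that the trial steering members know who is in HRV-G, because they pass the daily intensity to that group's coach. The article does not say that they are the researchers who judge cause.

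**4. Scale of one event**

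With 7 per group (section 2.5), one athlete is 1/7 = 14.3% of an arm. This shows how coarse the safety data are. It does not say how likely a lost event is.

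**The case against.** The strongest reply has four parts.

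- **The exception has a low threshold.** A serious event is reported if the study *may* have caused it, so a worsening training injury would probably qualify. This reduces the expected loss. It does not remove the dependence on an opinion, and it does nothing for events whose link to training is not recognised at the time.
- **A definition and a reporting period are different things.** This is correct. The fault is a reporting rule narrower than the definition, not a logical contradiction.
- **No safety comparison is stated.** Section 2.4 lists no safety outcome and section 2.8 no between-arm safety test. This stands, and it limits the consequence to incomplete reporting.
- **A condensed article may leave follow-up detail to the full protocol.** That answers a complaint about a missing follow-up window. It does not answer this point, which concerns a rule that the article does state.

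A reader might also infer three stronger claims that the text does not support.

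- *That events before the intervention are filtered out.* They are reported; only their attribution is preset.
- *That harms in the preparation period are automatically called unrelated.* This requires the intervention to begin only with the training period. One sentence can be read so: "In the TR period, each group will carry out the corresponding intervention". But section 2.3 first says that "the intervention will be divided into two training periods for both study groups", naming both the preparation and the training period. The later sentence most naturally refers to the arm-specific content.
- *That the harm which makes an athlete stop is lost.* It arises during participation and is collected. Only later serious events are at risk.

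**Conclusion.** The point holds in a limited form. For athletes who stop before the planned end, the written rule makes non-reporting of serious events the default and lets an opinion about cause, not stated to be blind to arm, decide the exceptions. This fits poorly with a definition that disregards cause and with an intention-to-treat claim over all data. Later worsening or new serious events in early leavers can go unreported.

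The number of events affected cannot be estimated, because the documents give no injury or dropout rate. The effect is a less complete safety record, with no bias shown in any stated result. A reader might go further and conclude that staff who know the arm are choosing what to report; the article does not identify the judges closely enough to support that.

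The conclusion assumes that stopping participation includes leaving before week 12, which the wording allows, and that exclusion under the 90% rule counts as stopping, which is likely but not stated. If the second assumption fails, the point still applies to athletes who leave by choice.

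**What to change.** In section 2.9, replace the post-stop sentence with a rule that:

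1. reports all serious adverse events, whatever their presumed cause, for every allocated athlete up to a fixed date, for example the planned week-12 post-test. This includes athletes who stop training, unless they have withdrawn consent to be contacted;
2. records causality as a separate field and not as a condition for reporting;
3. keeps the cause-based rule, if wanted, only for events after that date.

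As a secondary wording point, state that the study intervention in the pre-intervention attribution rule starts with week 1 of the preparation period, in line with the first sentence of section 2.3.

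The cost is a short amendment, one closing contact per leaver through the phone or email channel already used for daily HRV data (section 2.3), and a few more unrelated events on file. Sample size, training and outcome analysis do not change.

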### 2.10. Ethics and Dissemination

This protocol, the informed consent template contained in Appendix A and other requested documents (if any) will be reviewed and approved by the Bioethical Committee at the University of Almería with respect to the scientific content and compliance with applicable research and human subject regulations. Following initial review and approval, this protocol will be reviewed by the researcher at least once a year at Clinicaltrials.org, where it is registered with the ID: NCT04150952.

Any protocol modifications which might have an impact on conducting the study, potentially benefit a subject or affect a subject’s safety, or change the study objectives, study design, subject population, sample sizes, study procedures, along with significant administrative issues, will require a formal amendment to the protocol. Such an amendment will be agreed upon by the Bioethical Committee at the University of Almería prior to implementation, and the clubs/associations enrolled will be notified. Administrative changes to the protocol that are minor corrections, and/or clarifications having no effect on the way the study is to be conducted, will be agreed upon by the researchers and documented in a memorandum. The Bioethical Committee at the University of Almería may be notified of the administrative changes.

All study-related information will be stored securely at the study site. All records that contain names or other personal identifiers, such as locator forms and informed consent forms, will be stored separately from the study records and identified by a code number. Forms, lists, logbooks, appointment books and any other listings that link participant ID numbers to other identifying information will be stored in a separate, locked file.

